## Abstract

**Background:**

Hip replacement (arthroplasty) surgery is a highly successful treatment for patients with severe symptomatic arthritis of the hip joint. For older patients, several designs of Total Hip Arthroplasty have shown excellent results in terms of both function and value for money. However, in younger more active patients, there is approximately a 50% failure rate at 25 years for traditional implants. Hip resurfacing is a relatively new arthroplasty technique. In a recent review of the literature on resurfacing arthroplasty it was concluded that the short-term functional results appear promising but some potential early disadvantages were identified, including the risk of femoral neck fracture and collapse of the head of the femur.
The aim of the current study is to assess whether there is a difference in functional hip scores at one year post-operation between Total Hip Arthroplasty and Resurfacing Arthroplasty. Secondary aims include assessment of complication rates for both procedures as well cost effectiveness.

**Methods/design:**

All patients medically fit for surgery and deemed suitable for a resurfacing arthroplasty are eligible to take part in this study. A randomisation sequence will be produced and administered independently. After consenting, all patients will be clinically reviewed and hip function, quality of life and physical activity level will be assessed through questionnaires. The allocated surgery will then be performed with the preferred technique of the surgeon. Six weeks post-operation hip function will be assessed and complications recorded. Three, six and 12 months post-operation hip function, quality of life and physical activity level will be assessed. Additional information about patients' out-of-pocket expenses will also be collected.

**Trial registration:**

Current Controlled Trials ISRCTN33354155

UKCLRN portfolio ID 4093

## Background

Hip arthroplasty is a procedure which has been performed by orthopaedic surgeons for decades, with improvements to the procedure and the implants being made almost continuously over that time. For older patients, several designs of Total Hip Arthroplasty (THA) have shown excellent results in terms of both function and value for money [1]. However, in younger more active patients, there is an approximate 50% failure rate at 25 years for traditional implants [2]. Modern THA designs with hard bearing surfaces may improve upon these results [3], but long-term evidence is lacking. The early results of Resurfacing Arthroplasty (RSA), a new technique where the proximal femoral anatomy is preserved, suggest a 98% survival at five years [4]; which is as good as any of the existing THA's [1]. However, no long-term data exists. In a recent review of the literature on RSA it was concluded that although the short-term functional results appear promising, some potential early disadvantages were identified; including risk of femoral neck fracture, avascular necrosis of the head of the femur and acetabular bone stock sacrifice [5].

At present, only a few randomised trials have been performed comparing the traditional techniques of THA with the resurfacing technique. These studies have focused on the technical aspects of the procedure, such as the position of the implants or the amount of bone removed during the resurfacing procedure [6,7]. There are currently no published results of randomised trials comparing these two different methods of hip arthroplasty using hip function, activity level and patient quality of life as the primary outcome measure. In a non-randomised study, Pollard et al. [8] reported no difference in the Oxford hip score or the rate of revision between RSA and THA, however patients in the RSA group where shown to have higher activity levels after the procedure and were more likely to be involved in activities such as running and heavy manual labour. Furthermore, quality of life scores were found to be higher in the RSA group compared to the THA group. In another recent non-randomised study similar results were reported, with higher activity scores and range of movement scores for the resurfacing group [9]. In this study complication rates and reoperation rates at 2 year follow-up were the same for the two techniques, however the study design was poor as the two treatment groups were not comparable with regards to sex, age and pre-operative functional scores. To provide surgeons and patients with accurate information regarding early function and complication rates, we feel that it is essential to perform a randomised trial comparing THA with RSA.

The null hypothesis for this trial is that there is no difference in functional hip scores (Harris and Oxford Hip score) at one year post-operation between Total Hip Arthroplasty and Resurfacing Arthroplasty.

## Methods/design

### Design

This is a single-blind randomised controlled trial. This study has been reviewed by the Coventry Research Ethics Committee under reference number 07/Q2802/26. The study was approved on the 9^th ^of May 2007. The research carried out is in compliance with the Helsinki Declaration.

### Study participants

#### Inclusion criteria

The only eligibility criterion for participation in this study is that the patient is medically fit for an operation and suitable for a RSA (all patients that are suitable for RSA are also suitable for a THA). These broad eligibility criteria should ensure that the results of the study can readily be generalised to the wider population.

#### Exclusion criteria

Contra-indications to surgery, defined as: (i) severe cardiac impairment, e.g. heart or valve replacement, arrhythmia, previous myocardial infarction, (ii) severe respiratory impairment, e.g. chronic obstructive pulmonary disease, asthma that has required hospital admission, or (iii) any other systemic medical condition that would produce a specific contraindication to a general anaesthetic.

Evidence that the patient would be unable to adhere to trial procedures or complete questionnaires, such as dementia or intravenous drug abuse

If a recruited patient requires a contra-lateral hip replacement during the trial period, this second hip cannot be included in the study (i.e cannot be randomised) since the result of this intervention would not be independent from the first intervention.

#### Post randomisation withdrawals

Participants may withdraw from the trial at any time without prejudice. If patients decide to have the treatment to which they were not randomised, participants will be followed-up wherever possible and data collected as per the protocol until the end of the trial. The primary analysis will be on an intention-to-treat basis with a secondary per-protocol analysis. If patients decide to have neither treatment, they will be withdrawn from the trial and not included in the analysis.

The two treatments in this study are THA and RSA. Each patient will undergo the allocated surgery according to the preferred technique of the operating surgeon. The surgeons involved in the study use a variety of surgical approaches to the hip joint: anterolateral, posterior and, for the resurfacing patients, the Ganz approach. Some surgeons use an uncemented THA for younger more active patients whilst others prefer a more traditional cemented design or a 'hybrid' of the two. In the same way, some surgeons cement the femoral component of a RSA while others prefer an uncemented component.

In summary, the details of the surgery will be left entirely to the discretion of the supervising surgical consultant to ensure that the results of the trial can be generalised to as wide a group of patients as possible.

### The Study intervention

#### Total Hip Arthroplasty

In a THA, the femoral head is removed along with the majority of the femoral neck. The femoral shaft is 'reamed' to open up the femoral canal. The femoral component is then inserted into the canal and the articulating femoral head is placed onto the neck of the femoral component.

#### Resurfacing Arthroplasty

In a RSA, the articular surfaces of the femoral head are removed but the neck is left in-situ. The femoral component is then impacted onto the patient's own femoral neck.

In both forms of Arthroplasty, the acetabulum is reamed and the acetabular component inserted into the 'socket'. The radiograph (Figure 1) shows a THA on the right side and a RSA on the left side.

**Figure 1 F1:**
[figure not shown]
**X-ray showing a Total Hip Arthroplasty (THA) and a Resurfacing Arthroplasty (RSA)**.

#### Rehabilitation

Standardised rehabilitation plans will be implemented for all of the patients; as outlined in the University Hospitals Coventry and Warwickshire NHS Trust 'Hip Replacement: A Guide for Patients' booklet. This includes information on early exercises, precautions to be followed for the first three months, functional activity and later stage exercises. A photocopy of the 'joint rehabilitation discharge letter' will be made as proof that all of the patients completed these tasks to a standard level before discharge.

#### Follow-up

Patients will continue in routine clinical follow-up, as per their surgeon's practice. For this trial, the primary outcome point will be at one year, with other planned assessments at six weeks, 3 months and six months after operation. At all these occasions patients will come to the clinic to be reviewed by the research associate and if necessary a doctor.

### Study objectives

There are three main objectives of this randomised controlled trial:

1. To quantify and draw inferences on observed differences in primary and secondary outcomes measures between the trial treatment groups at one year post-operatively.

2. To detemine the complication rate of Resurfacing Hip Arthroplasty versus Total Hip Arthroplasty at one year post-operatively.

3. To investigate, using appropriate statistical and economic analysis methods, the resource use, and thereby the cost effectiveness, of Resurfacing Hip Arthroplasty versus Total Hip Arthroplasty.

### Outcome measures

This study has two primary outcome measures; the ***Oxford Hip Score ***[10] and the ***Harris Hip Score ***[11]. The Oxford Hip Score is a validated questionnaire which is self-administered. It consists of 12 items related to daily tasks directly influenced by poor hip function. The Harris Hip score is also a hip function questionnaire which includes items reflecting a patient's ability to perform normal daily activities but also contains objective measurements such as range-of-movement.

Three secondary outcome measures will be used in this trial; (i) ***EuroQol 5D (EQ-5D)***: A validated quality of life questionnaire consisting of 5 questions related to daily activities scored on a 3-point ordinal score scale. Answers can be combined using published algorithms to obtain health-related quality of life values (ii) ***Disability Rating Index***, a self-administered, 12-item VAS questionnaire assessing the patient's own rating of disability and (iii) ***Paffenbarger Physical Activity Questionnaire***, this questionnaire assesses the number of calories a patient expends on leisure and physical activities built on an assessment of energy spent on average week and weekend days, as well as additional energy spent during sporting activities throughout the year. All complications will be recorded during the course of the trial.

Resource use will be monitored for the economic analysis. NHS costs associated with each arm of the trial will be estimated using data from both national sources (NHS reference costs, PSSRU reference costs [12]) and the finance departments of the hospitals and services concerned. The cost consequences following discharge, including NHS costs and patients' out-of-pocket expenses will be recorded via a short questionnaire which will be administered at 3, 6 and 12 months post surgery. Patient self-reported information on service use has been shown to be accurate in terms of intensity of use of different services [13].

In this study, we will use techniques common in long term cohort studies to ensure minimum loss at recruitment, such as collection of multiple contact addresses and telephone numbers, mobile telephone numbers and email addresses. Every possible effort will be made to minimise loss to follow-up, with a target of complete follow-up. Using these techniques, we are confident that loss will not exceed 10%. In the event of a participant being lost to the final follow-up at one year, we will consider, on the advice of the trial statistician, imputing missing primary outcome data from interim scores.

A system of reminders will be instituted to ensure that return to clinic at three, six and twelve months is as complete as possible. The Research Associate will phone participants to make an appointment, after two weeks non-response a letter will be send out to the patient. The letter will be followed up by phone call after 1-2 weeks. If there is no response from the participant, they will be classed as a 'non-responder' and the case closed.

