### Sample size

Previous work has shown the Oxford Hip Score (OHS) and the Harris Hip Score (HHS) to be reliable measures of hip function after surgery, as measured by Cronbach's alpha statistic for internal consistency [10,14]. Correlation analysis has indicated that both measures are reproducible, i.e. their test-retest reliability is good, and previous studies [15] have shown them to be strongly correlated, indicating that both scoring systems are measuring the same latent characteristic (hip function). However, the self-administered OHS has achieved much higher follow-up rates than the more widely used HHS [15]. Therefore, in order to provide the best assessment of patient experience of hip function after surgery and also to allow dissemination of the results of this trial to as wide a potential audience as possible in resulting publications, we prudently choose to use both the OHS and the HHS as primary outcome measures.

Harris Hip Score. There is less available specific information on previously observed variability for the HHS, than for the OHS. Assuming Normally distributed scores, the required numbers of patients in each arm of the trial are shown in Table 1, based on an independent samples t-test (at the 5% level) for assumed standard deviations (SD) of 13 and 15 [15] and minimum clinically important differences (MCIDs) of 7 and 10 [16](PS, power and sample size software, available at http://biostat.mc.vanderbilt.edu/wiki/Main/PowerSampleSize

**Table 1 T1:** Patient number required for MCID in Harris Hip Score at different power levels.

	MCID = 7		MCID = 10	
**Power**	**80%**	**90%**	**80%**	**90%**

SD				

13	**55**	**73**	28	37

15	73	97	36	48

MCID: Minimum clinically important difference

The minimum clinically important differences used for this sample size calculation give effect sizes of around 0.6; a medium to large effect size using the conventional descriptions of these terms [17]. More reliable data for determination of the MCID is available for the OHS.

Oxford Hip Score. The best estimate for the standard deviation for the OHS is 9 and the MCID is between 5 and 7 points on the OHS scale, calculated from a previous comprehensively reported study [18]. Using these estimates the required numbers of patients in each arm of the study, for a two-sample t-test (at the 5% level) are shown in Table 2.

**Table 2 T2:** Patient number required for minimum MCID in Oxford Hip Score at different power levels.

	MCID = 5		MCID = 7	

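### The reminder rule does not limit closure to the missed visit; read literally, non-response at 3 or 6 months ends follow-up before the 12-month primary outcome

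*Protocol article*

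**What the plan says.** The rule stands in the loss-to-follow-up text under Outcome measures in the protocol article. Its scope is three visits: "A system of reminders will be instituted to ensure that return to clinic at three, six and twelve months is as complete as possible". Contact begins with a phone call from the research associate to arrange attendance. If this brings no reply, "after two weeks non-response a letter will be send out to the patient". A second call is due one to two weeks later. The sequence ends: "If there is no response from the participant, they will be classed as a 'non-responder' and the case closed".

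Four other statements bear on it:

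- Follow-up section: "the primary outcome point will be at one year". Statistical analysis places the primary t-tests at 12 months.
- Outcome measures, the paragraph before the rule: "Every possible effort will be made to minimise loss to follow-up, with a target of complete follow-up". The authors add that "we are confident that loss will not exceed 10" percent.
- Same paragraph: for a patient lost at one year, imputing the primary outcome from earlier scores will be considered on the statistician's advice.
- Sample size: "the self-administered OHS has achieved much higher follow-up rates than the more widely used HHS".

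**The concern.** The closing sentence classifies the participant, not the visit. It has no qualifier confining it to the visit being chased and no provision for reopening. A research associate who follows it to the letter would stop contacting a patient after about three to four weeks of silence (two weeks to the letter, one to two more to the second call), even if this happens at month 3, nine months before the primary assessment.

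Temporary non-response at an interim visit would then become permanent loss of both primary outcomes in an intention-to-treat trial. It would also remove the 12-month EQ-5D value and any later interim value that the within-trial QALY calculation needs. That works against the stated aim of full follow-up. The loss would be avoidable, because the trial already collects several addresses, phone numbers and email addresses for each patient.

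**Working it through.** **1. The plan's own figure.** Inputs from Sample size: Harris Hip Score (HHS) difference 7, SD 13; Oxford Hip Score (OHS) difference 5, SD 9; 90% power; 5% level (taken as two-sided). An exact two-sample t-test gives 73.5 (HHS) and 69.1 (OHS) per arm, against the stated 73 and 69. Adding the upper end of the stated 2-5 patients for multiplicity gives 73 + 5 = 78 per arm, 156 in total. With the drop-out allowance, 156 × 1.1 = 171.6, so 172 as stated. This point contests none of these figures.

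**2. What remains after closure.** The abstract places hip function assessments before surgery, at six weeks, and at 3, 6 and 12 months. Under the literal reading:

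| Closed at | Post-operative hip scores available, at most | 12-month outcome |
|---|---|---|
| 3 months | six weeks | not sought |
| 6 months | six weeks, 3 months | not sought |
| 12 months | six weeks, 3 and 6 months | sought, not obtained |

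Imputation from interim scores therefore has very little to work with after closure at 3 months, and somewhat more after closure at 6.

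**3. Possible size of the loss.** The protocol gives no per-visit rate of final non-response. Call it q and assume it is the same at all three visits.

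- Closure of the visit only: 12-month loss = q.
- Permanent closure, same patients unreachable every time: 12-month loss = q, so no excess.
- Permanent closure, non-response independent across visits: 12-month loss = 1 − (1 − q)³.

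| Assumed q | Visit-only closure | Permanent closure: same patients to independent |
|---|---|---|
| 2% | 2% | 2% to 5.9% |
| 5% | 5% | 5% to 14.3% |
| 10% | 10% | 10% to 27.1% |

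At q = 5% under independence, 1 − 0.95³ = 0.143. Also under independence, the 10% allowance is passed once q exceeds 1 − 0.9^(1/3) = 3.45%.

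**4. Effect on power at q = 5%, with 172 randomised.** Visit-only closure leaves 172 × 0.95 / 2 = 81.7 per arm. Permanent closure under independence leaves 172 × 0.95³ / 2 = 73.7 per arm. The 2.5% level is the first Holm-Bonferroni step.

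| Outcome and level | Visit-only (81.7 per arm) | Permanent, independent (73.7 per arm) |
|---|---|---|
| HHS, 5% | 93% | 90% |
| HHS, 2.5% | 88% | 84% |
| OHS, 5% | 94% | 92% |
| OHS, 2.5% | 90% | 86% |

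At the planned 10% loss (172 × 0.9 / 2 = 77.4 per arm), HHS power at 2.5% is already 86%. Most of the gap to 90% at that level comes from the multiplicity adjustment, not from the closing rule.

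**The case against.** The strongest reply is that closing the case may mean only that the chasing for that appointment stops. The sentence ends a paragraph about one appointment sequence. The Follow-up section schedules the one-year assessment without making it depend on earlier attendance, and the stated aim of full follow-up favours the narrower reading. This stands in part: the narrower reading is possible. But the sentence does not say so, its grammatical subject is the participant, and the person applying it could follow either reading.

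A reader might infer that any missed 3- or 6-month visit discards the 12-month outcome. The document does not support that. The trigger is silence after a call, a letter and a second call, so a patient who answers but misses the appointment is not a non-responder. Nor does the text say that later visits are cancelled or that data are thrown away.

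A reader might also take the 14% as the expected loss. It rests on independence between visits. If the same patients are unreachable each time, closure adds nothing.

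That non-response depends on hip function, which would make the loss informative, is plausible, but nothing in the document establishes it.

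Finally, tying follow-up to clinic return is not itself an error: the HHS is co-primary and includes range of movement, and back-up modes of collection are detail that an article may leave to the full protocol.

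**Conclusion.** The point holds as a defect in a stated rule. The protocol applies closure after a reminder system covering three visits, does not confine it to the visit concerned, and so permits follow-up to end before the primary outcome is measured. That sits in conflict with its stated aim of full follow-up, and the imputation under consideration would do little for a patient closed at 3 months.

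The size cannot be fixed from the document. With an assumed 5% final non-response per visit, the excess 12-month loss from permanent closure runs from nil to about 9 percentage points (14.3 − 5), or up to about 16 of 172 patients. The loss of power is modest, at most about 4 percentage points for either score at the 2.5% level. The case for a change rests on avoidable missing primary outcome data, not on power. It should be corrected, but it does not undermine the design.

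**What to change.** Replace the closing sentence with a rule that:

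- non-response after the call, letter and second call closes that visit only;
- every patient who has not withdrawn is contacted again at each later visit, and at 12 months whatever happened before;
- if clinic attendance at 12 months fails, the self-administered OHS, EQ-5D and other self-report forms are sought by post, email or phone before the patient is classed as a non-responder.

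The last item is a sensible fallback, and the protocol's own remark on the better follow-up of the OHS supports it. It would not rescue the HHS in full, because the range-of-movement part needs a visit.

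The cost is one or two sentences, a few extra letters and calls by existing staff using contact details already collected, and some OHS data obtained by a different mode. The mode should be recorded for each 12-month form.

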### Sample size

Previous work has shown the Oxford Hip Score (OHS) and the Harris Hip Score (HHS) to be reliable measures of hip function after surgery, as measured by Cronbach's alpha statistic for internal consistency [10,14]. Correlation analysis has indicated that both measures are reproducible, i.e. their test-retest reliability is good, and previous studies [15] have shown them to be strongly correlated, indicating that both scoring systems are measuring the same latent characteristic (hip function). However, the self-administered OHS has achieved much higher follow-up rates than the more widely used HHS [15]. Therefore, in order to provide the best assessment of patient experience of hip function after surgery and also to allow dissemination of the results of this trial to as wide a potential audience as possible in resulting publications, we prudently choose to use both the OHS and the HHS as primary outcome measures.

Harris Hip Score. There is less available specific information on previously observed variability for the HHS, than for the OHS. Assuming Normally distributed scores, the required numbers of patients in each arm of the trial are shown in Table 1, based on an independent samples t-test (at the 5% level) for assumed standard deviations (SD) of 13 and 15 [15] and minimum clinically important differences (MCIDs) of 7 and 10 [16](PS, power and sample size software, available at http://biostat.mc.vanderbilt.edu/wiki/Main/PowerSampleSize

**Table 1 T1:** Patient number required for MCID in Harris Hip Score at different power levels.

	MCID = 7		MCID = 10	
**Power**	**80%**	**90%**	**80%**	**90%**

SD				

13	**55**	**73**	28	37

15	73	97	36	48

MCID: Minimum clinically important difference

The minimum clinically important differences used for this sample size calculation give effect sizes of around 0.6; a medium to large effect size using the conventional descriptions of these terms [17]. More reliable data for determination of the MCID is available for the OHS.

Oxford Hip Score. The best estimate for the standard deviation for the OHS is 9 and the MCID is between 5 and 7 points on the OHS scale, calculated from a previous comprehensively reported study [18]. Using these estimates the required numbers of patients in each arm of the study, for a two-sample t-test (at the 5% level) are shown in Table 2.

**Table 2 T2:** Patient number required for minimum MCID in Oxford Hip Score at different power levels.

	MCID = 5		MCID = 7	
**Power**	**80%**	**90%**	**80%**	**90%**

Sample size	**52**	**69**	27	36

MCID: Minimum clinically important difference

The results for the OHS and the HHS at the 5% significance level, based on the best available estimates of MCID (5 and 7 score points respectively) are very similar. Both scores are intended to measure patient hip function, so it is not unexpected that the sample sizes obtained using these scores give very similar results. An adjustment to the significance level for multiple comparisons resulted in only a small increase (2-5 patients) in the required numbers.

In summary, this study will use two primary outcome measures the Oxford Hip Score and the Harris Hip Score. The aim will be to recruit 78 patients in each group as this will provide sufficient participants to obtain a power of 90% for both primary outcome measures. With an allowance for 10% drop-out, the total number of patients required will be **172**. If recruitment proves to be problematic during the course of the trial, then with the agreement of the trial steering committee the target will be lowered and the more usual 80% power level will be considered sufficient. For this scenario, the total number of patients required will be 120 (including 10% for drop-out).

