### Statistical analysis

The main analysis will investigate differences in the primary outcome measures, the Harris Hip Score and the patient-reported Oxford Hip Score, between the two treatment groups on an intention-to-treat basis. The differences between treatment groups will be assessed using an independent samples t-test at 12 months post-operatively at the 5% level. Test levels, for the two primary outcome measures will be adjusted using the methods of Holm-Bonferroni [19] to allow for the multiple comparisons. A linear regression analysis will also be used to quantify the effects of the treatment groups on each of the primary outcome measures, after adjusting for the effects of a range of other important, potentially confounding, factors (e.g. age, gender) recorded for each patient. Subsidiary analyses will report results of tests for secondary outcome measures and primary outcome measures at interim occasions. Interim analyses will be performed only where directed by the Data Monitoring Committee.

The second main statistical objective of the trial is to determine, and compare, the complication rate of RSA and THA at one year post-operatively. All complications will be recorded during the trial, and rates will be determined at 12 months post-operatively and compared between treatment groups using a chi-squared (at the 5% level).

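### The stated cost of 2-5 patients for multiplicity does not reproduce at the 2.5% first Holm step (about 11-13 more per arm), and the 90% power for both scores rests on conditions the protocol does not state

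*Protocol article*

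**What the plan says.** The Sample size section sizes each primary outcome with a two-sample t-test at 5%. For the HHS it tabulates requirements "for assumed standard deviations (SD) of 13 and 15 [15] and minimum clinically important differences (MCIDs) of 7 and 10", after noting: "There is less available specific information on previously observed variability for the HHS, than for the OHS". For the OHS, "The best estimate for the standard deviation for the OHS is 9", with a minimum important difference (MCID) of 5 to 7. The bold entries, per arm for 80% and 90% power, are 55 and 73 for the HHS (7, SD 13) and 52 and 69 for the OHS (5, SD 9).

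On two primary outcomes the section adds: "An adjustment to the significance level for multiple comparisons resulted in only a small increase (2-5 patients) in the required numbers". It then sets 78 per group because "this will provide sufficient participants to obtain a power of 90% for both primary outcome measures", and 172 in total after a 10% drop-out allowance.

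The Statistical analysis section says: "The differences between treatment groups will be assessed using an independent samples t-test at 12 months post-operatively at the 5% level", and then: "Test levels, for the two primary outcome measures will be adjusted using the methods of Holm-Bonferroni [19] to allow for the multiple comparisons".

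The article gives no adjusted level, no value for the correlation between the scores (it calls it strong), and no definition of 90% for both.

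**The concern.** With two tests, Holm-Bonferroni compares the smaller p-value with 2.5%. Halving the level usually costs far more than a handful of patients at these sample sizes. The 2-5 figure also seems to drive the target, since the larger bold 90% entry plus five is 73 + 5 = 78; the article does not state this sum, so it is an inference.

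If the increment is too small for the named method, the 90% claim depends on something unstated. A reader who later sees one score significant and the other not, or neither, will judge that result against 90% power. That reader needs to know whether 90% applies to each score or to both jointly, and what it assumes.

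**Working it through.** **Inputs.** From Sample size: HHS difference 7, SD 13 (alternative 15); OHS difference 5, SD 9; 78 per arm. From Statistical analysis: t-test, 5% overall, Holm-Bonferroni over two outcomes. Assumed here: two-sided tests (this reproduces the tables), the 2-5 read as per arm like the tables, and a correlation of 0 to 0.9 because none is given.

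**Formula.** Per arm, n ≈ 2 (SD/δ)² (z for the level + z for the power)². The exact figures below use the noncentral t.

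**Step 1: the protocol's own tables at 5%, 90% power.**
- HHS: 2 × (13/7)² × (1.960 + 1.282)² = 72.5; exact 73.45. Table 1 has 73.
- OHS: 2 × (9/5)² × (1.960 + 1.282)² = 68.1; exact 69.06. Table 2 has 69.
- At 80% power the exact values are 55.12 and 51.84, against 55 and 52.

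The tables reproduce. So does the total: 2 × 78 = 156, and 156 × 1.1 = 171.6, or 172.

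**Step 2: the same at 2.5%.** The z-value rises from 1.960 to 2.241.

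| Score, power | n at 5% | n at 2.5% | Increase |
|---|---|---|---|
| HHS (7, SD 13), 80% | 55.12 | 66.84 | 11.7 |
| HHS (7, SD 13), 90% | 73.45 | 86.88 | 13.4 |
| OHS (5, SD 9), 80% | 51.84 | 62.87 | 11.0 |
| OHS (5, SD 9), 90% | 69.06 | 81.70 | 12.6 |

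In whole patients, 90% power needs 87 (HHS) and 82 (OHS). The smallest increase in any cell of Tables 1 and 2 is about 6 (OHS difference 7, 80% power: 27 to 33). No cell gives 2-5. If the 2-5 meant both arms together, the gap would be wider.

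**Step 3: power at 78 per arm, fixed level.**
- HHS: 91.6% at 5%, 86.3% at 2.5%.
- OHS: 93.2% at 5%, 88.5% at 2.5%.

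**Step 4: the planned Holm procedure at 78 per arm.** A score is significant if its p ≤ 2.5%, or if its p ≤ 5% and the other's p ≤ 2.5%. By simulation, with both differences real:

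| Correlation | HHS | OHS | Both |
|---|---|---|---|
| 0 | 91.1% | 92.5% | 85.1% |
| 0.5 | 90.4% | 91.7% | 86.5% |
| 0.7 | 90.0% | 91.3% | 87.4% |
| 0.9 | 89.5% | 90.5% | 88.6% |

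On this basis 90% for each score needs 76-80 (HHS) and 72-77 (OHS) per arm, which is 3-8 above the table values. For both together, 90% needs 82-88. If only one score differs, its Holm power is close to its 2.5% figure: about 86% (HHS) or 88-89% (OHS).

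**Step 5: HHS SD, separate from multiplicity.** With difference 7 and SD 15, HHS power at 78 per arm is 82.5% unadjusted, about 81% under Holm with both differences real, and 74.2% at 2.5%. Table 1 itself requires 97 per arm for this SD at 5%.

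**The case against.** The strongest defence is that the planned test is Holm, not a fixed 2.5% test, and the article never says the sizing was done at 2.5%. It describes the scores as strongly correlated measures of the same characteristic and sizes each at its own MCID, so both scores differing is the natural design alternative. On that alternative 78 per arm does give about 90% for each score, and the increase of 3-8 overlaps 2-5. A correlation-adjusted level near 4% (assumed correlation 0.6-0.8) would also give about 2-5. All of this stands as a defence of the target. It does not rescue the sentence. The text speaks of adjusting the significance level, gives neither level nor correlation, and a correlation-adjusted level is not the Holm-Bonferroni method the analysis names.

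It is also fair to say that the SD 15 shortfall does not come from multiplicity and is open to view in Table 1. It belongs beside this point as a separate note.

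A reader might infer more: that the trial is under-powered in every scenario but one, that joint power never reaches 90%, or that the target must rise to 87. The documents do not support this. At the larger tabulated MCIDs, 78 per arm is ample even at 2.5%: 97% for the HHS (10, SD 15) and 99.5% for the OHS (7). Joint Holm power with HHS 10, SD 15 and OHS 5 is about 92-93%. The shortfalls belong to the smaller MCIDs on which the target was set.

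**Conclusion.** The point holds at the planning MCIDs (HHS 7 with SD 13, OHS 5 with SD 9). The 2-5 increment does not follow from the 2.5% first step of the named method; the increase there is about 11-13 per arm. The 90% claim is right for each score separately (HHS 89-91%, OHS 91-93%) only when both scores differ by these amounts and the step-down is used. For a score that differs alone it is about 86% (HHS) or 88% (OHS), and as joint power it is 85-89%, so it is not met on that reading. The Holm ranges rest on an assumed correlation of 0-0.9.

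This is an unsupported increment and an undefined power claim. It is not evidence that 78 per arm is the wrong target, and with SD 13 the single-score shortfall is modest: 90 − 86.3 = 3.7 points for the HHS and 90 − 88.5 = 1.5 for the OHS.

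**What to change.** 1. Replace the 2-5 patients sentence in Sample size with the 2.5% figures (HHS 67 and 87, OHS 63 and 82 per arm for 80% and 90% power). Alternatively, keep a small increment but state that it assumes the Holm step-down with both effects present, and give the assumed correlation.
2. State that 90% for both means each score separately. Beside it, report 86% (HHS) and 88% (OHS) at the first step, and 85-89% for both together.
3. As a separate note, say that the 90% for the HHS at difference 7 rests on SD 13 and falls to about 81% under Holm (83% unadjusted) if the SD is 15.

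The target of 78 per arm and the total of 172 need not change. The cost is a few sentences and a slightly less favourable power statement.
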